## Abstract

**Background:**

An unhealthy eating pattern and loneliness negatively influence quality of life in older age. Embodied conversational agents (ECAs) are a promising way to address these health behaviors in an engaging manner.

**Objective:**

We aim to (1) identify whether ECAs can persuade community-dwelling older adults to change their dietary behavior and whether ECA use can decrease loneliness, (2) test these pathways to effects, and (3) understand the use of an ECA.

**Methods:**

The web-based eHealth app PACO is a fully automated 8-week intervention in which 2 ECAs engage older adults in dialogue to motivate them to change their dietary behavior and decrease their loneliness. PACO was developed via a human-centered and stakeholder-inclusive design approach and incorporates Self-determination Theory and various behavior change techniques. For this study, an unblinded randomized controlled trial will be performed. There will be 2 cohorts, with 30 participants per cohort. Participants in the first cohort will immediately receive the PACO app for 8 weeks, while participants in the second cohort receive the PACO app after a waiting-list condition of 4 weeks. Participants will be recruited via social media, an online panel, flyers, and advertorials. To be eligible, participants must be at least 65 years of age, must not be in paid employment, and must live alone independently at home. Primary outcomes will be self-assessed via online questionnaires at intake, control, after 4 weeks, and after 8 weeks, and will include eating behavior and loneliness. In addition, the primary outcome—use—will be measured via data logs. Secondary outcomes will be measured at the same junctures, via either validated, self-assessed, online questionnaires or an optional interview.

**Results:**

As of July 2020, we have begun recruiting participants.

**Conclusions:**

By unraveling the mechanisms behind the use of a web-based intervention with ECAs, we hope to gain a fine-grained understanding of both the effectiveness and the use of ECAs in the health context.

**Trial Registration:**

ClinicalTrials.gov NCT04510883; https://clinicaltrials.gov/ct2/show/NCT04510883

**International Registered Report Identifier (IRRID):**

PRR1-10.2196/22186

## Introduction

### Background

Unhealthy eating and loneliness negatively influence quality of life (QoL) in older age [1,2]. Statistics show that in the Netherlands, almost 60% of people over 65 are obese [3], and 57% of community-dwelling older adults are at risk for undernutrition [4]. Both are important risk factors for chronic diseases and are clearly associated with unhealthy eating behaviors. As eating is regarded as a social activity, loneliness is associated with a loss of pleasure in eating and cooking [5] and is a significant predictor of malnutrition [6]. Loneliness can be defined as the discrepancy between a person’s desired and achieved levels of social relationships [7]. In the Netherlands, over 50% of older adults indicate that they experience loneliness, a percentage that is even higher among people without a partner [8]. The expected increase in the coming years [9] in this group of single, community-dwelling older adults will exacerbate this problem. However, it is challenging to realize an actual change in eating behavior and deal with loneliness.

Embodied conversational agents (ECAs) have been proposed as a promising technological tool to persuasively address these health behaviors, with the aim of changing users’ attitudes or behaviors through persuasion and social influence rather than through coercion [10]. ECAs can be defined as “more or less autonomous and intelligent software entities with an embodiment used to communicate with the user” [11]. A typical user interface consists of a human-like ECA with prewritten dialogues, including multiple choice answer options [12]. ECAs can make an intervention for coaching people in a healthy lifestyle more engaging than traditional electronic health interventions [12]. This ability is often ascribed to ECAs’ capacity to establish and maintain an emphatic relationship [12,13]. Early studies show that older adults who interact with an ECA form a relationship with the ECA and consider it a companion [14], including those from populations in which eHealth literacy is generally lower [15]. ECAs are perceived as enjoyable, usable, and acceptable for addressing health behavior change [16-18].

Nonetheless, interventions with an ECA are not immune to declining use over time, meaning that this issue must be addressed in ECA design to prevent limited long-term health effects [12]. Furthermore, and even more importantly, evidence of ECA effectiveness and underlying working mechanisms is scarce and remains inconclusive [12]. This limits the possibility to learn from others’ efforts and prevents knowledge accumulation.

### Objectives

We present the protocol for an 8-week evaluation of the PACO service. Consisting of 2 ECAs, PACO is a web-based app that aims to achieve dietary behavior change and decrease loneliness among single, community-dwelling older adults. The goal of the evaluation is to (1) identify whether ECAs can persuade community-dwelling older adults to change their dietary behavior and decrease their loneliness, (2) assess the pathways to effects, and (3) understand ECA use. The latter 2 goals will allow us to explain the occurrence (or the lack) of an effect from using the intervention and can therefore serve to support the design of future ECAs.

### Conceptual Models

In order to conceptualize and measure engagement, Cole-Lewis et al [19] state that it is necessary for users to have appropriate levels of interaction with the technology and that the behavioral change components are relevant. Hence, we present 2 conceptual models. The first is a conceptual model explaining ECA use (CEU; Figure 1). With this model, we aim to explain the factors that determine the use of an ECA intervention in this context. The second is a conceptual model explaining health effects (CHE; Figure 2). With this model, we aim to explain the mechanisms behind the observed change in eating behavior and loneliness.

**Figure 1 figure1:**
[figure not shown]
Conceptual model explaining embodied conversational agents (ECA) use, known as CEU.

**Figure 2 figure2:**
[figure not shown]
Conceptual model explaining health effects, known as CHE.

Use is at the center of the conceptual model explaining ECA use. It is assumed that an eHealth intervention will not be used if it does not create any benefit (perceived usefulness) or if it has a substantial number of usability problems [20]. Visual aesthetics, defined as an orderly and clear design, are closely related to many of the design rules advocated by usability experts [21]. In the case of patient portals, aesthetics have thus been found to influence usability in the context of explaining technology acceptance [22]. We expect perceived usefulness to be influenced by 3 user experience factors. Perceiving something as enjoyable is linked to a positive effect on use when the system is perceived to be useful [23]. Willingness to share personal information and preferences (ie, the absence of privacy concerns) is argued to be a prerequisite for convenience and a useful system [24]. The last factor is control, which refers to “the extent to which the user can bring about or prevent particular actions or states of the system if she has the goal of doing so” [25]. Especially in human-computer interaction literature, control has been identified as a crucial factor in the occurrence of perceived usefulness and use [26,27]. Furthermore, there is robust evidence that usability has a direct effect on perceived usefulness [28]. In turn, use is hypothesized to act as an antecedent of the intensity of an end user’s relationship with an ECA [14].

Self-determination Theory (SDT) comprises the basis of the conceptual model explaining health effects [29]. Briefly, SDT postulates that human beings have 3 essential psychological needs: autonomy (the feeling of being the origin of one’s own behaviors), competence (feeling effective), and relatedness (the need to feel belongingness and connectedness with others). Self-monitoring and self-efficacy are associated with increased autonomy [30]. Tailoring is a more generic behavior change technique (BCT), which, in our case, refers to a tailored recipe book. We hypothesize that the possibility of generating a tailored recipe book leads to an increased feeling of being in control. Action planning is found to be supportive of increasing competence [31]. Both social learning and social facilitation are expected to lead to an increase in relatedness, as they both connect people. In turn, a decrease in loneliness and an improvement in eating behavior is expected to lead to more positive health-related QoL outcomes [1,2].

### Research Questions

Our research questions focus on both use and health outcomes. The research questions related to use are as follows: (1) What factors affect the use of the ECA? (2) Does use affect the users’ relationship with the ECA? (3) What is the use of PACO over time? (4) How do users experience PACO use? We will test the CEU to answer research question (RQ) 1 and 2. Via data log analyses (RQ3) and interviews (RQ4) we aim to explain the findings related to the CEU. This way, we will triangulate results.

The research questions related to health effects are as follows: (1) To what extent does PACO reduce loneliness and improves eating behavior and, ultimately, QoL? (2) To what extent does PACO increase autonomy, competence, and relatedness? (3) How does PACO use affect the loneliness and eating behavior of older adults? We will test the CHE to answer RQ1. For RQ2 and RQ3, we will compare the effect of using PACO at different time points, including control.

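### Health RQ1, an effect question, is assigned to a mechanism model (the CHE) with no arm or exposure contrast described, and no stated analysis uses the randomised contrast

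*Protocol article*

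**What the plan says.** All references are to the protocol article.

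- **Research Questions.** Health RQ1 reads "To what extent does PACO reduce loneliness and improves eating behavior and, ultimately, QoL". RQ2 asks how far PACO raises autonomy, competence and relatedness. RQ3 reads "How does PACO use affect the loneliness and eating behavior of older adults".
- **Assignment of analyses, same section.** The mapping is stated as "We will test the CHE to answer RQ1. For RQ2 and RQ3, we will compare the effect of using PACO at different time points". The Control measurement is counted among those time points.
- **Conceptual Models.** The purpose of the CHE is given as "we aim to explain the mechanisms behind the observed change in eating behavior and loneliness". Its antecedents are behaviour change techniques, for example "Self-monitoring and self-efficacy are associated with increased autonomy". The chain then runs through the three psychological needs to eating and loneliness, and on to quality of life (QoL). The text names no cohort, arm or exposure term. Figure 2, which draws the model, is not shown.
- **Objectives.** Goal 1 is the effect on diet and loneliness. The other two goals are listed separately: "2) assess the pathways to effects, and (3) understand ECA use".
- **Study Design and Procedure.** Cohort 2 waits 4 weeks and serves as the control group. It alone completes the additional Control questionnaire.
- **Table 1.** Eating behaviour, loneliness, the three needs and QoL are all measured at Control, T0, T1 and T2.
- **Data Analysis.** A within-subject t test compares Control, T0, T1 and T2. PLS-SEM tests the two conceptual models; the waves or change scores that enter it are not stated.

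**The concern.** RQ1 covers two of the trial's primary outcomes, loneliness and eating behaviour. It asks for the size of an effect, and that requires a contrast between having PACO and not having it. The analysis assigned to it is a path model whose stated purpose is to explain a change already observed. A path from relatedness to loneliness describes how the two vary together across people, and it can be present whether or not PACO works.

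RQ3 asks how use affects the outcomes. Its natural reading is the mechanism question, yet it goes to comparisons of means over time, which cannot show a pathway.

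The consequence is practical. Participants are randomised to immediate or delayed access, but the one test stated for means is within-subject. An analyst who follows the article as written never sets the randomised cohorts against each other to answer RQ1.

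**Working it through.** **1. The plan's own figure.** The Participants section bases 60 (30 per cohort) on the 10-times rule: N ≥ 10 × the largest number of paths into one construct. That number is not stated. The text suggests at most 4 in the model of use (enjoyment, privacy concerns, control and usability into perceived usefulness), so 10 × 4 = 40. It suggests at most 3 in the CHE (self-monitoring, self-efficacy and tailoring into autonomy), so 10 × 3 = 30. Sixty would need 6 paths, or the other considerations that the section mentions. The figure meets the minimum but cannot be reproduced exactly. The point here does not depend on it.

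**2. Question against analysis.**

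| Question | What it asks | Assigned analysis | Fit |
|---|---|---|---|
| RQ1 | Size of effect on loneliness, eating, QoL | CHE | Conflicts with the stated purpose of the CHE |
| RQ2 | Size of effect on the three needs | Time-point comparisons, control included | Suitable type, but within-subject |
| RQ3 | How use affects loneliness and eating | Time-point comparisons, control included | Poor fit if read as mechanism; partial fit if read as effect of use |

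**3. What a path among app users says about the effect.** If PACO shifts loneliness Y by a constant δ in every user, then corr(M, Y + δ) = corr(M, Y) for any predictor M. The correlation does not depend on δ. A simulation illustrates this under assumed values: 30 per cohort, relatedness–loneliness correlation −0.5 at the start, correlation 0.7 between successive loneliness measurements, 4,000 runs. The correlation among exposed participants was −0.29 with a true effect of 0 and −0.29 with a true effect of −0.5 SD. The week-4 between-cohort contrast gave about 0.00 and −0.50.

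**4. Chance of a significant path with no PACO effect.** Power ≈ Φ(atanh(r) × √(n − 3) − 1.96), with n = 60 and √57 = 7.55. The correlations are assumptions; the document gives none.

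| r | atanh(r) × 7.55 | Chance of significance |
|---|---|---|
| 0.2 | 1.53 | 0.33 |
| 0.3 | 2.34 | 0.65 |
| 0.4 | 3.20 | 0.89 |
| 0.5 | 4.15 | 0.99 |

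This uses a simple correlation in place of a PLS path with several predictors, and it lets all 60 contribute. It shows an order of magnitude only.

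**5. Whether within-subject comparisons replace the randomised contrast.** A before–after change estimates effect plus drift. In the same simulation, with an assumed drift of −0.3 SD per 4 weeks, the mean change was −0.30 with no effect. With a true effect of −0.50 it was −0.80 (−0.50 − 0.30). The between-cohort contrast stayed at about 0.00 and −0.50.

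**6. Precision of the randomised contrast.** Assume 30 per cohort, two-sided 5%, SD 1, no dropout and no adjustment. The difference detectable with 80% power is (1.960 + 0.842) × √(2/30) = 2.802 × 0.258 = 0.72 SD. Power is 0.21 at d = 0.3, 0.49 at d = 0.5 and 0.87 at d = 0.8. Adjustment for first measurement multiplies the detectable difference by √(1 − ρ²). With an assumed ρ of 0.7, that is 0.72 × 0.71 ≈ 0.52.

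**The case against.** The best defence is that an effect analysis exists under another label. The comparisons for RQ2 and RQ3 explicitly include control, and cohort 2 contributes an unexposed period. RQ3 names loneliness and eating, two of RQ1's three outcomes. The Data Analysis section does not limit the t tests to particular outcomes, and QoL is measured at every wave. RQ3 can also be read as asking about the effect of use. RQ1's closing reference to QoL mirrors the last link in the CHE, which may be why the two were paired. RQ2 is given a suitable type of analysis.

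Much of this stands. Three stronger readings are therefore not supported:

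- **That the CHE has no unexposed group.** Figure 2 is not shown, the data entering PLS-SEM are not specified, and every measured CHE construct is also collected at Control. The text supports only that no arm or exposure contrast is described for it.
- **That neither analysis answers its question.** Time-point tests will bear on loneliness and eating, and possibly on QoL.
- **That a significant path would be reported as proof that PACO works.** That is a prediction; the t tests remain a separate analysis.

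Two things survive the defence. RQ1 is expressly sent to the CHE, against the article's own account of that model. And the comparisons that could stand in for it are stated as within-subject. QoL is named only under RQ1, so its only assigned analysis is the CHE.

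**Conclusion.** The point holds as a mismatch between question and analysis, with a real consequence for the effect conclusion. RQ1 is assigned to a model that the article describes as explanatory and for which its text describes no arm or exposure contrast. RQ3, if it is a mechanism question, is assigned to comparisons that cannot show a mechanism. No stated analysis uses the randomised contrast.

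The size is illustrative. Paths could reach significance with no PACO effect in roughly a third of samples to nearly all of them, depending on a correlation that the document does not give. The relevance of this range to RQ1 assumes that the CHE is fitted without an exposure term, which the text suggests but does not state. The mismatch itself rests on the article's wording and needs no numerical assumption.

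**What to change.** **Change the mapping in Research Questions and match it in Data Analysis.**

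- Answer RQ1 (loneliness, eating, QoL) and RQ2 (the three needs) with the randomised week-4 comparison: cohort 1 at T1 against cohort 2 at T0. Adjust for first measurement (cohort 1 at T0, cohort 2 at Control) and report the difference with a confidence interval.
- Say whether the 14-day inactivity rule applies to this comparison. Before week 4 it could remove people only from cohort 1, so the comparison should keep everyone with a week-4 answer.
- Answer RQ3 with the CHE. State which waves or change scores enter it, and report its paths as associations.
- Keep the within-subject comparisons as descriptions of change over the 8 weeks.

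A fully time-ordered version of the CHE is one option, but it is a preference and not needed to correct the mapping.

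**Cost.** Wording only; every measurement is already planned. Precision is modest, with 80% power only for about d = 0.7 before adjustment, so intervals matter more than p-values. The randomised comparison covers only the first 4 weeks of use, so results at 8 weeks remain uncontrolled. As the Procedure section reads, participants learn their cohort before the first measurement, so the adjustment assumes that this knowledge did not change their answers.

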## Methods

### Study Design

An unblinded randomized controlled trial will be carried out. At the time of study protocol submission, all preparations have been made to start recruitment. There will be 2 cohorts (Figure 3). Participants in the first cohort will receive the 8-week PACO app immediately. Participants in the second cohort will receive the PACO app after a 4-week waiting-list condition and serve as a control group. A combination of various data collection methods will be used for this study, including questionnaires (control, at intake, T0, T1, and T2), data log collection during the intervention period, and an optional interview afterward. The T0 questionnaire will mark the start of the intervention, T1 will be completed after 4 weeks of use, and T2 after 8 weeks of use (Figure 3).

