### Procedure

Interested people can visit a website to view more information, or they can contact the researchers. People can choose to receive the information letter and consent form by post (Multimedia Appendix 1) or view and complete the form online. After providing informed consent, participants will be invited to complete the intake questionnaire. In this questionnaire, they will be asked to report their demographics (gender, age, educational level, health conditions, risk of malnutrition [35], and eHealth literacy [36]), whether they own a device to use for the study, and their motivation to participate. A copy of the signed informed consent will be sent to all participants by mail. The researchers will mail people who do not return the informed consent by post to check whether something has gone wrong or they do not wish to participate (no explanation will be required).

After completing both the informed consent and the intake questionnaire, participants will be assigned a random 4-digit research number. To allocate participants to a cohort, they will be randomly assigned a digit, either 1 or 2, in a list generated by Excel (version 16.0.13426.20274; Microsoft). Participants will receive an email from author LK containing their research number, information on their allocated cohort, and a copy of the information letter and the signed informed consent.

Participants in cohort 2 will first be asked to complete the additional control questionnaire (Table 1) and will start the intervention period after 4 weeks. At the start of the intervention period, participants will receive an email with instructions for the onboarding process. The email will contain a video message from the researchers introducing themselves and the project, as well as a link to the freely available PACO website. Once participants have created an account, they will be asked to complete the T0 questionnaire, assessing the health parameters and relationship with the ECA. Participants will be phoned within 2 working days and asked whether they have any questions. If a participant does not wish to be called, this can be indicated by email. If a participant needs help, the researchers will offer to visit the participant. A logbook will be kept of all such contacts. If participants do not have a tablet or a computer, they will be given a tablet for the duration of the study.

**Table 1 table1:** Metadata and factors measured via questionnaires, per study phase.

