### Intervention

#### PACO App

PACO is a fully automated web-based eHealth app in which 2 ECAs engage in dialogue with older adults in order to motivate them to change their dietary behavior and decrease their loneliness (Figure 4 and Multimedia Appendix 2). The app consists of 5 modules, each one applying different BCTs (Table 2). During the onboarding process, the ECAs introduce themselves and explain the PACO program. There is a daily dialogue between either Herman (the cook, who provides nutritional advice) or Ellen (the peer, who provides social advice) and the user. Users are asked to use the food diary module for the first 7 days in order to increase their awareness of their eating behavior. All other modules become available when the food diary has been completed for 7 days or automatically after 14 days. During and after the 8-week program, the ECAs encourage users to continue the health behavior changes that they have implemented during the intervention in their daily lives.

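### The wait-list is 4 weeks and the programme 8, so no unexposed group remains after week 4 and within-person change from T0 to T2 is uncontrolled; the article should limit its controlled effect claim accordingly

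*Protocol article*

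**What the plan says.** Study Design sets the two arms: "Participants in the first cohort will receive the 8-week PACO app immediately", and "Participants in the second cohort will receive the PACO app after a 4-week waiting-list condition and serve as a control group". Procedure confirms that cohort 2 "will start the intervention period after 4 weeks". The questionnaires follow use, not calendar time: "T1 will be completed after 4 weeks of use, and T2 after 8 weeks of use". The control questionnaire is given to cohort 2 only.

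Objectives opens with "We present the protocol for an 8-week evaluation of the PACO service". The first health research question asks "To what extent does PACO reduce loneliness and improves eating behavior and, ultimately, QoL" and is to be answered by testing the health-effects model. The second and third are to be answered by comparing time points, control included. Data Analysis names a within-subject t test across control, T0, T1 and T2. Limitations discusses recruitment, contamination and use driven by the study itself, but not the length of the wait.

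On content, PACO App states "The app consists of 5 modules, each one applying different BCTs". After the food diary, it says "All other modules become available when the food diary has been completed for 7 days or automatically after 14 days". Table 2 instead lists Recipes, Stories and Chat for weeks 1-8 and Goals for weeks 2-8. The modules that Table 2 links to loneliness are Goals, Stories and Chat.

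**The concern.** The control period is half as long as the programme it is meant to control. Loneliness and eating behavior are main study parameters, and the evaluation is presented as one of 8 weeks. A T0-T2 difference from a within-subject test has no unexposed comparison behind it, yet it stands in the same analysis sentence as the control measurement and nothing marks it as different. It would be natural to report it as the effect of the programme.

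Such a change also contains things that are not PACO: drift over time, regression to the mean if people enrol at a bad moment, and attention from the researchers. That attention is real here. Participants are phoned at the start, contacted after 7 days without interaction and visited on request, and Ethical Considerations notes that participants in prior studies valued it.

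A second question is how much of the loneliness content falls inside the controlled window, since the unlock rule holds back four of the five modules at first.

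**Working it through.** **Inputs.** Programme 8 weeks = 56 days and wait 4 weeks = 28 days (Study Design). Cohort 2 starts use at week 4 (Procedure). T1 and T2 come after 4 and 8 weeks of use (Study Design). The other modules unlock after 7 completed diary days at the earliest and after 14 days at the latest (PACO App). Listed weeks per module are in Table 2. The article gives no figure for controlled exposure, so there is none to reproduce.

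**Calendar.** Week 0 is taken as cohort 1's T0 and cohort 2's control questionnaire.

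| Week | Cohort 1 | Cohort 2 | Contrast between cohorts |
|---|---|---|---|
| 0 | T0, no use | Control, no use | baseline |
| 4 | T1, 4 weeks of use | T0, no use | use against no use |
| 8 | T2, 8 weeks of use | T1, 4 weeks of use | 8 against 4 weeks of use |
| 12 | none | T2, 8 weeks of use | none |

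The last exposed-versus-unexposed contrast is at week 4. Programme days without an unexposed comparator: 56 - 28 = 28, and 28/56 = 50%.

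**Controlled access to the loneliness modules.** Controlled days = 28 - unlock day; days by T2 = 56 - unlock day.

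| Reading | Modules | Controlled days | Days by T2 | Share |
|---|---|---|---|---|
| Unlock rule, earliest | Goals, Stories, Chat | 28 - 7 = 21 | 56 - 7 = 49 | 21/49 = 43% |
| Unlock rule, latest | Goals, Stories, Chat | 28 - 14 = 14 | 56 - 14 = 42 | 14/42 = 33% |
| Table 2, from week 1 | Stories, Chat | 28 | 56 | 28/56 = 50% |
| Table 2, from week 2 | Goals | 28 - 7 = 21 | 56 - 7 = 49 | 21/49 = 43% |

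Across both readings the range is 14 to 28 days. The locked part of the controlled window under the unlock rule is 7/28 = 25% to 14/28 = 50%.

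**What the between-cohort contrasts estimate.** Let d4 and d8 be the effects of 4 and 8 weeks of use.

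- Week 4: cohort 1 T1 minus cohort 2 T0 estimates d4.
- Week 8: cohort 1 T2 minus cohort 2 T1 estimates d8 - d4.
- Sum: d4 + (d8 - d4) = d8.

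The sum equals d8 only if 4 weeks of use has the same effect whether it starts at week 0 or at week 4. It also costs precision. Assume equal variances and a correlation r between a person's two measurements. Each contrast then has variance 2s²/n and their covariance is 2rs²/n, so the sum has variance (2s²/n)(2 + 2r). Its standard error is √(2 + 2r) times that of one contrast: 1.41 times at r = 0 and 2 times at r = 1. The article gives no r.

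**What the named test estimates.** A within-subject T0-T2 comparison gives d8 plus any change over those 8 weeks not due to PACO. No randomised comparison enters it.

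**The case against.** The strongest reply is that a 4-week wait is a legitimate choice in a study the article calls explorative, and that no sentence promises an unexposed comparison at week 8. That stands. The first health research question names no time point. A reader might infer a broken promise of a controlled result at T2, but the text does not make that promise.

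A reader might also infer that no analysis can recover an 8-week effect. That is too strong: the two between-cohort contrasts add up to d8 under the start-time assumption, using questionnaires already planned, and 8 against 4 weeks of use is informative in itself. Cohort 2's own change over the wait also shows 4 weeks of drift, though using it for 8 weeks means extrapolating. None of this rescues the within-subject T0-T2 comparison.

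Three further inferences about the loneliness content go beyond the documents. That the controlled window is mostly diary run-in: the run-in takes at most half of it. That controlled access is 2 to 3 weeks as a settled fact: Table 2 gives 4 weeks for Stories and Chat. That week 4 is therefore likely to show little effect on loneliness: the article gives no dose-response or time-to-effect figure, and the daily dialogue, which includes the social-advice agent, is not stated to be locked. For eating behavior, the food diary is available throughout the 28 days.

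An unseen analysis plan may name a between-cohort test. It could not create unexposed participants after week 4.

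**Conclusion.** The concern holds in limited form. Exposed-versus-unexposed comparison ends at week 4, half of the programme has no unexposed comparator, and the named within-subject analysis would let uncontrolled T0-T2 change pass as an effect of PACO. This follows from the stated calendar and does not depend on how the modules unlock. It assumes only that cohort 1 starts at about the time cohort 2 starts waiting.

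The module figures are secondary and conditional: 14 to 21 controlled days under the unlock rule, up to 28 for Stories and Chat under Table 2. They are days of access, not estimates of bias or power. The two descriptions conflict, and the documents do not show which applies.

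Even the week-4 contrast compares PACO together with its researcher support against waiting. It deals with time trends and regression to the mean, but does not separate the app from the attention.

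**What to change.** 1. State in Objectives and Data Analysis that the controlled effect claim rests on the week-4 between-cohort contrast, cohort 1 at T1 against cohort 2 at T0.
2. State that T0-T2 within-person change is uncontrolled and will not be reported as an effect of PACO.
3. If an 8-week effect is derived by adding the week-4 and week-8 between-cohort contrasts, label it as relying on the assumption that 4 weeks of use has the same effect whenever it starts.
4. Reconcile the unlock rule in PACO App with the weeks in Table 2, and report each participant's logged days of module access at T1.

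The cost is wording, one descriptive summary from data logs already planned, and a narrower claim. No extra participants or questionnaires are needed.

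Lengthening the wait to 8 weeks would give an unexposed comparator at week 8. It would also extend cohort 2 from 4 + 8 = 12 to 8 + 8 = 16 weeks, risk drop-out during the wait and change a design that is approved, registered and recruiting. It is an optional trade-off, not a required change.
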